### Outcome Measures

The primary outcome of this study is a reduction in pain intensity in the lumbosacral region and legs (radiating pain) perceived by participants, assessed as the change in the 10 cm VAS score at day 30 and after 3 months from baseline.

The secondary outcomes of this study are improvement in functional disability due to LDH, assessed by the ODI, version 2.0; change in neurodynamic evaluation, assessed using the SLRT; improvement in QoL, assessed by the SF-36; comparison of dependence on allopathic analgesics; and assessment of safety and acceptability of the *marma* therapy in patients with LDH, assessed by the incidence of adverse events (AEs) associated with the therapy and compliance of patients to *marma* therapy.

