### Participant Timeline

Eligible participants, upon signing the informed consent form, are assessed for screening according to the criteria outlined in the study protocol. Spine examination and neurological assessment by a spine surgeon, systemic examination, SLRT, MRI of the lumbosacral spine, and laboratory investigations (including hemogram, liver function test, renal function test, C-reactive protein, hemoglobin A1c, random blood sugar, rheumatoid factor, and human leukocyte antigen B27 test) are done during the screening of participants before baseline evaluation. Patients undergoing any internal or external therapy or Ayurvedic medication for pain management are instructed to discontinue these treatments, and a baseline evaluation is conducted after a 1-week washout period.

At the baseline visit, general information for personal identification and demographic profiling is collected, medical history is recorded, and a clinical examination for general physical and systemic conditions is done, followed by a detailed neurological examination. Assessment of pain by the 10 cm VAS, functional disability by the ODI, and QoL using the SF-36 is done. The history of consumption of nonsteroidal anti-inflammatory drugs (NSAIDs) or analgesic medications during the last 14 days is also noted. The Ayurvedic parameters, such as *prakriti*, are also assessed at baseline.

The participants are assigned the treatment as per group allocation mentioned on the chit in the opaque sealed envelopes opened by the participant upon baseline evaluation. Each study participant is called daily for the assigned therapy (*marma* therapy or physiotherapy) for 4 weeks. Oral medication has continued for 12 weeks.

Follow-up and outcome assessments are conducted on days 7, 15, 21, 30, 45, 60, and 90. Any AE reported by a study participant is recorded at each visit and thoroughly assessed for causality. Ongoing events are managed through appropriate interventions, including referral to a higher center when necessary. A telephonic follow-up on day 75 is done to note any AEs, the need for rescue medication, and drug compliance. Details of assessments done during each visit of the study participant are given in Table 1.

**Table 1. T1:** Participant timeline.

Variable	Study period									
	Enrollment	Allocation	After allocation							
	Screening	Baseline	Day 7	Day 15	Day 21	Day 30	Day 45	Day 60	Day 75 (telephonic)	Day 90
Enrollment										
Information and written consent	✓									

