### Data Analysis

After verification for accuracy, all collected data will be anonymized prior to statistical analysis. All analyses will follow both the intention-to-treat and per-protocol principles to evaluate the robustness and sensitivity of the results. Any missing or incomplete responses will be addressed through Bayesian imputation. To make the imputation robust, regression-based imputation will also be applied if sufficient information is available in the data. Furthermore, the data will be used for descriptive analysis. Categorical variables will be described as frequencies and percentages, while continuous variables will be summarized as mean (SD) or median (IQR), depending on the distribution of the data (normal or skewed). Inferential analyses will be performed after descriptive analysis of the data. For within-group comparisons, data will be analyzed using the paired 2-tailed t test or the Wilcoxon signed-rank test, depending on the distribution of the data for pre-post observations. Between-group comparisons will be performed using the independent-samples *t* test or Mann-Whitney *U* test, depending on the normality of the data.

Repeated-measures ANOVA or the Friedman test will be used for within-group and between-group analyses of the outcomes assessed at multiple time points. The generalized estimating equation and the repeated-measures ANOVA, along with factor analysis, will also be performed if any confounding factors are found during the analysis. Analysis of covariance will be performed if baseline differences between groups are observed. A 2-sided significance level of 5% will be considered for all analyses. All statistical analyses will be performed using Stata software (version 16.1; StataCorp).

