## Results

Participant recruitment was initiated on April 4, 2022, and as of November 2025, a total of 90 patients have been enrolled. Of these, 70 (77.8%) study participants have completed the final follow-up. Data cleaning is now complete, and the results will be published once the analysis is complete. The final report and data interpretation are expected to be submitted for publication in 2026.

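### The Friedman test is assigned to between-group analysis of the repeated outcomes, but it has no group term and cannot compare the two arms

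*Protocol article*

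**What the plan says.** Four statements in the Protocol article, Data Analysis, bear on how the arms are compared:

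- For single comparisons: "Between-group comparisons will be performed using the independent-samples" t test or the Mann-Whitney U test, the choice "depending on the normality of the data".
- For repeated outcomes: "Repeated-measures ANOVA or the Friedman test will be used for within-group and between-group analyses of the outcomes assessed at multiple time points".
- Generalized estimating equations, again with repeated-measures ANOVA, "will also be performed if any confounding factors are found during the analysis".
- Adjustment for baseline is conditional too: "Analysis of covariance will be performed if baseline differences between groups are observed".

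Outcome Measures defines the primary outcome as pain reduction "assessed as the change in the 10 cm VAS score at day 30 and after 3 months from baseline". Participant Timeline adds: "Follow-up and outcome assessments are conducted on days 7, 15, 21, 30, 45, 60, and 90". With baseline, that gives eight VAS measurements. Table 1 also ticks pain assessment at the day-75 telephone contact. ODI, SF-36 and straight leg raise are ticked at baseline and days 15, 30, 60 and 90. All of these outcomes therefore fall under the repeated-outcomes sentence.

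That sentence does not say what decides between ANOVA and Friedman. The sentences just before it choose between parametric and nonparametric tests by the distribution of the data, so the natural reading is that Friedman applies when the data look non-normal.

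**The concern.** The Friedman test is a one-sample repeated-measures test. It asks whether the visits differ within a single set of participants. This is a two-arm parallel trial, and the between-group question is whether the arms differ. On the nonparametric branch, the sentence hands that question to a test that cannot answer it.

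The consequence is specific to this trial. Both arms take the same oral formulation for 12 weeks, both may use rescue analgesics, and each receives an active therapy for 4 weeks. Pain is expected to fall in both arms whatever marma therapy adds over physiotherapy. A Friedman result will therefore very probably be significant, and under the sentence as written it could carry a between-group label. A bounded pain score can well be skewed, so this branch is a realistic route.

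**Working it through.** The plan attaches no figure to this rule, so there is none to reproduce. The check is on what the test can detect.

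**Inputs.** From the document: two parallel arms (Study Design); SD 1.36 and 72 evaluable participants, that is 72/2 = 36 per arm (Sample Size); baseline plus seven visits, so k = 8 (Participant Timeline); two-sided 5% level (Data Analysis). Assumed, because the document does not give them: within-participant correlation 0.5, equal for all visit pairs, and a mean VAS falling from 6.5 to 3.05. The end value is the post-treatment mean cited under Sample Size. The 72 only sets the scale of the simulation; nothing here depends on how it was derived.

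**Step 1: the formula.** Let r_ij be the rank of visit j among participant i's own k values, and R_j the sum of r_ij over all N participants. Without ties,

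Q = [12 / (N k (k+1))] × Σ R_j² − 3N(k+1).

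With N = 72 and k = 8: 12/(72 × 8 × 9) = 1/432 and 3 × 72 × 9 = 1,944, so Q = Σ R_j²/432 − 1,944. Arm membership appears nowhere in it.

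**Step 2: a constant shift.** Ranks are taken within a participant, so a constant added to all of that participant's values changes nothing. Scores of 6, 5 and 3 rank 3, 2, 1; lowered by 3 points they become 3, 2 and 0, and still rank 3, 2, 1. In one simulated data set, Q was 310.07. After 3 points were subtracted from every value in one arm, Q was again 310.07. Analysing change from baseline does not help, since subtracting the baseline is also a constant within each participant.

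**Step 3: rejection rates** over 2,000 simulated trials per scenario (Monte Carlo standard error near 5%: √(0.05 × 0.95/2000) = 0.5 percentage points).

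| Scenario | Friedman, arms pooled | t test, day 30 | t test, day 90 |
|---|---|---|---|
| Both arms improve, no group difference | 100% | 5.5% | 5.5% |
| Both improve, 1-point difference at every post-baseline visit | 100% | 87.1% | 86.9% |
| No change over time, constant 1-point difference | 4.7% | not run | not run |

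The first two rows show that Friedman gives the same answer with and without a group difference, while a two-sample test at the named visits separates them. The third row shows that it responds to time and not to group. The t tests here use the VAS score itself. With correlation 0.5 the SD of change is 1.36 × √(2 × (1 − 0.5)) = 1.36, so tests on change have essentially the same power.

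**Step 4: running it in each arm.** Applied separately in each arm, Friedman also rejected in about 100% of trials, with no group difference and with a 1-point difference alike. Two within-arm p values set side by side are not a between-group test in any case.

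**The case against.** The strongest reply is that the trial does not depend on this sentence. The sentence immediately before it names the t test or Mann-Whitney U test for comparing groups, and the primary outcome is a change score at two named visits. Mann-Whitney on that change is a valid nonparametric comparison and needs no repeated-measures method. With a 1-point benefit that builds up to day 30 and then holds, and the same SD and correlation, Mann-Whitney on the day-90 change has about 85% power and the t test on change about 87%, both above the planned 80%. This stands. A reader might infer that skewed data leave the plan with no valid between-group test at all; the document does not support that.

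Three further inferences are tempting and also fail:

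- *That repeated-measures ANOVA cannot address day 30 or month 3.* It can carry contrasts at those visits, and these may be set out in an analysis plan that is not shown.
- *That the ANOVA route costs a known amount of power.* Such a figure would have to look only at the group main effect, ignore the group-by-time test, and take baseline as one of the repeated levels. The document says none of this.
- *That participants without a final visit will be dropped.* Results reports that "70 (77.8%) study participants have completed the final follow-up", but Data Analysis plans imputation of missing responses and an intention-to-treat analysis.

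It is also fair to say that the 100% rejection rate is not the false-positive rate of the primary comparison. It shows only that the test detects change over time. That a Friedman result would be reported as efficacy is a risk created by the wording, not something the document states it will do.

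None of this rescues the sentence itself. It gives the Friedman test a between-group role, and an unseen analysis plan cannot supply a group term. Generalized estimating equations could compare arms over time, but they are invoked only if confounding is found. The section does not say which named test decides, so the invalid one stands beside the valid ones with equal status.

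**Conclusion.** Wrong as written, and limited to the between-group use of the Friedman test. On the nonparametric branch, the repeated-measures comparison of arms for VAS, ODI, SF-36 or straight leg raise would be a test of time under a between-group label.

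That conclusion rests on the form of the statistic and needs no assumption about correlation, profile or sample size. Only the simulated percentages depend on the assumed correlation of 0.5 and the assumed improving profile. The practical size depends on whether the data are judged non-normal and on which test is then presented as the comparison of arms; the document settles neither. The single-visit tests and the repeated-measures ANOVA branch are not faulted here.

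**What to change.** In Data Analysis:

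1. Restrict the Friedman test to describing change over visits within an arm.
2. For between-group analysis of the repeated outcomes, name one model with group, visit, group-by-visit and baseline score, for example a linear mixed model on the post-baseline visits. Report the group difference with its 95% CI at day 30 and day 90, the time points that Outcome Measures already sets.
3. If the data are skewed, compare the arms on change at those two visits by a valid rank-based or resampling method, such as Mann-Whitney U, rank-ANCOVA or a permutation test.

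The cost is analysis wording. No new data are needed, and Stata, the software already named, fits such a model. Protocol Amendments already provides for reporting changes in analysis methods to the sponsor and the ethics committee. Results says that data cleaning is complete and analysis is under way, so the change should be dated and fixed before any comparison by arm is seen. If one has already been seen, the report should say so.

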## Methods

### Participants, Interventions, and Outcomes

#### Study Design

This is a randomized, open-label, parallel-arm, active-controlled clinical trial.

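### Adjustment is conditional on confounders or baseline differences found in the data, factor analysis is named as part of it, and no between-group analysis is designated primary

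*Protocol article*

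**What the plan says.** All of the relevant text is in the Data Analysis section of the protocol article.

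- Default comparison: "Between-group comparisons will be performed using the independent-samples *t* test or Mann-Whitney *U* test, depending on the normality of the data".
- Several time points: "Repeated-measures ANOVA or the Friedman test will be used for within-group and between-group analyses of the outcomes assessed at multiple time points".
- First conditional adjustment: GEE and repeated-measures ANOVA, "along with factor analysis, will also be performed if any confounding factors are found during the analysis".
- Second conditional adjustment: "Analysis of covariance will be performed if baseline differences between groups are observed".
- Order of work: "Inferential analyses will be performed after descriptive analysis of the data".
- Error level: "A 2-sided significance level of 5% will be considered for all analyses".

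The section lists no covariates, does not define a confounder or a baseline difference, and does not call any between-group analysis primary. The Study Design section describes the trial thus: "This is a randomized, open-label, parallel-arm, active-controlled clinical trial". The Results section reports where the data stand: "Data cleaning is now complete, and the results will be published once the analysis is complete".

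**The concern.** There are three separate problems.

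1. **The trigger.** Randomisation means that baseline factors differ between arms only by chance. The reason to adjust is that a variable predicts the outcome, which can be judged beforehand. A search for confounders while the analysis is under way makes adjustment depend on the data. As worded, the search is not limited to baseline variables.
2. **The tool.** Factor analysis condenses correlated variables into latent factors. It does not estimate a treatment effect or adjust one. The authors may have meant a model with several factors, but the text does not say so.
3. **Precedence.** Unadjusted tests, repeated-measures methods, GEE and ANCOVA can all address the same pain comparison, each at 5%. If they disagree, the article does not say which one answers the primary question.

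At stake are precision, if adjustment happens only when a trigger fires, and control of type I error, if the reported model can be chosen freely.

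**Working it through.** The plan gives no figure for this point beyond its two-sided 5% level, so the check asks what happens to that 5%, and to power, under different readings of the text.

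**A. Type I error**

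Inputs from the article: 45 per arm (Sample Size) and two-sided 5% (Data Analysis). Assumed: no treatment effect; a unit-variance outcome; baseline-outcome correlation r of 0.3, 0.5 or 0.7; and four further independent baseline covariates, each with coefficient 0.2. There were 20,000 simulated trials at r = 0.5 and 8,000 at each of the others. Simulation error near 5% is √(0.05 × 0.95 / 20,000) = 0.15 and √(0.05 × 0.95 / 8,000) = 0.24 percentage points.

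| Procedure | r = 0.3 | r = 0.5 | r = 0.7 |
|---|---|---|---|
| Fixed t test | 4.9% | 4.8% | 4.9% |
| Fixed ANCOVA on baseline | 4.9% | 4.9% | 4.9% |
| ANCOVA only if baseline differs at p < 0.05 | 4.8% | 4.3% | 3.5% |
| Adjust for covariates that shift the estimate by more than 10% | 4.4% | 3.8% | 4.0% |
| Smaller p value of t test and ANCOVA | 6.3% | 7.1% | 8.0% |
| Smallest p value of 7 models | 10.0% | 10.9% | 13.1% |

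The 7 models are the unadjusted one, one for each of the five covariates alone, and one with all five.

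Rows 1 and 2 reproduce the nominal level. Rows 3 and 4 apply a rule without regard to the treatment p value; they stay at or below 5%. Only rows 5 and 6, which select by p value, exceed it.

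**B. Precision given up when adjustment is conditional**

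Inputs from the Sample Size section: difference 1 point, SD 1.36, and 72 participants before attrition, so 72 / 2 = 36 per arm. Assumed: the same SD at baseline and follow-up, and correlation r between them.

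- SD of change = 1.36 × √(2(1 − r)).
- Residual SD after ANCOVA = 1.36 × √(1 − r²).
- Standard error = SD × √(2/36).
- Approximate power = Φ(1/SE − 1.96).

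For r = 0.3:
- t test on change: SD 1.609, SE 0.379, 1/SE = 2.64, power Φ(0.68) = 75%.
- ANCOVA: SD 1.297, SE 0.306, 1/SE = 3.27, power Φ(1.31) = 90%.

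For r = 0.5:
- t test on change: SD 1.360, SE 0.321, 1/SE = 3.12, power Φ(1.16) = 88%.
- ANCOVA: SD 1.178, SE 0.278, 1/SE = 3.60, power Φ(1.64) = 95%.

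Simulation with t-based tests agrees within about a point: 74% against 89% at r = 0.3, and 88% against 94% at r = 0.5. The gain shrinks as r rises; at r = 0.7 the same formulas give 98% against 99%.

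**C. What the text leaves open**

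Table 1 has rescue medication and compliance recorded from day 7, after randomisation. Outcome Measures lists analgesic dependence as a secondary outcome. Nothing in Data Analysis prevents such a variable from being treated as a confounder. Treatment may affect analgesic use, so conditioning on it would distort the estimated effect on pain.

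**The case against.** Several points on the other side have force.

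- **The conditional models are additional.** The article says that they are also to be performed, and the t test or Mann-Whitney comparison is stated without that condition. A reader might infer that the efficacy model itself will be chosen after seeing the outcome data. The text does not say so. It fails only to say which result decides.
- **Most choices carry a trigger.** Normality, a baseline difference or a confounder steers the choice, so this is not a free pick among interchangeable tests. The triggers have no criteria, however.
- **Type I error need not rise.** A reader might infer that any data-dependent adjustment inflates it. Rows 3 and 4 of the table show otherwise. The 6% to 13% range requires selection by p value, which the article nowhere plans.
- **Adjustment for rescue analgesics or compliance is not proposed.** It is only not excluded.
- **Open-label treatment does not establish bias here.** Under Assignment of Interventions, the assessors of the primary outcome, functional disability and neurodynamic evaluation are described as unaware of allocation. Nor does open-label treatment show that the analyst is unblinded.
- **An unseen analysis plan may rank the models.** This answers part of the precedence point. It does not answer the rest: the article positively states a rule of looking for confounders during the analysis and names factor analysis for it. A plan that fixed covariates in advance would contradict that sentence.

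**Conclusion.** The point holds as a rule that the article states and fixes badly. Adjustment should not wait for confounders or baseline differences to appear, factor analysis is the wrong tool, and the deciding between-group analysis is not identified.

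The more certain cost is precision. At the planned 36 per arm, a t test on change has about 15 points less power than baseline-adjusted ANCOVA at r = 0.3 and about 6 points less at r = 0.5. These losses rest on assumed correlations and on equal SDs at both times. The inflation of type I error to roughly 6% to 13% is a hypothetical worst case for the covariate structures tried. The documents do not support stating it as the trial's expected error rate.

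This should be changed, but it does not by itself invalidate the trial.

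**What to change.** Replace the conditional adjustment sentences before the analysis is run:

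1. Name one primary between-group analysis that always adjusts for the baseline value of the outcome, for example ANCOVA or a repeated-measures model with baseline as a covariate. The choice between these is the authors'.
2. Name any further baseline covariates in advance. The acute, subacute or chronic category recorded at baseline (Table 1) is one option; the article does not show it to be prognostic.
3. Label the unadjusted test and GEE as sensitivity analyses.
4. State that no post-randomisation variable, such as rescue analgesic use or compliance, enters the efficacy model. Analgesic dependence and compliance are already covered in the secondary outcomes.
5. Delete factor analysis.

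The cost is wording only. The baseline data are already collected and the sample size does not change; fixed ANCOVA held about 4.9% type I error in the simulation. One caution on timing: the Results section has the analysis still to be completed, while the abstract calls it ongoing. The change should therefore be dated, with a statement of whether any between-group results had been seen.

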### Sample Size

A previous study that included physiotherapy as an intervention reported a mean VAS score for back pain of 3.05 (SD 1.36) points after treatment [11]. This was considered to anticipate an improvement of at least 2.79 points after *marma* therapy. Assuming a between-group difference of 1 point, with 80% power at 5% level of significance, the derived sample size was 72 participants. Furthermore, assuming a 20% attrition rate, the final sample size for this study was 90 participants, randomly allocated to the 2 groups in a 1:1 ratio (n=45, 50% participants per group). The effect size will be determined after the data analysis is completed.

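### Baseline adjustment depends on an undefined observed imbalance, which gives up precision that adjusting in all cases would keep

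*Protocol article*

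**What the plan says.** Outcome Measures defines the primary outcome as pain intensity, "assessed as the change in the 10 cm VAS score at day 30 and after 3 months from baseline". For the comparison of arms, Data Analysis gives this default: "Between-group comparisons will be performed using the independent-samples *t* test or Mann-Whitney *U* test, depending on the normality of the data". It adds that "Repeated-measures ANOVA or the Friedman test will be used for within-group and between-group analyses of the outcomes assessed at multiple time points". No baseline covariate is stated for any of these. Adjustment enters through one conditional sentence: "Analysis of covariance will be performed if baseline differences between groups are observed". The article does not say which baseline variable is meant, how a difference is judged, or how large it must be. Nowhere is a baseline-adjusted model made the analysis regardless of balance.

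The data for such a model exist. At the baseline visit, before the allocation envelope is opened, "Assessment of pain by the 10 cm VAS, functional disability by the ODI, and QoL using the SF-36 is done".

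**The concern.** The rule ties adjustment to the wrong thing. Under concealed 1:1 randomisation any baseline difference between arms arises by chance. The reason to adjust is that baseline pain predicts later pain, and that holds whether or not the arms look different. A rule that adjusts only after an imbalance is seen has three consequences:

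- It gives up precision in every trial where the trigger does not fire.
- It leaves imbalance below the trigger in the estimate.
- Because the trigger is undefined, the choice of model is left until the data are in view.

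The article fixes this rule itself, so it is not a detail left to a separate analysis plan.

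**Working it through.** **Inputs from the article.** Sample Size cites an earlier physiotherapy study that "reported a mean VAS score for back pain of 3.05 (SD 1.36) points after treatment", and continues: "Assuming a between-group difference of 1 point, with 80% power at 5% level of significance, the derived sample size was 72 participants". Data Analysis states: "A 2-sided significance level of 5% will be considered for all analyses". Allocation is 1:1, so 72 evaluable participants means n = 36 per arm.

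**Assumptions, not in the article.** SD 1.36 at baseline as well as at follow-up; correlation ρ between them of 0.3 to 0.7; a single-visit comparison; a trigger rule, since none is defined.

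**Step 1: the plan's own figure.** n per arm = 2(1.96 + 0.842)² × 1.36² / 1² = 29.03, so 30 per arm and 60 in total (62 with the t distribution). The stated 72 is not reproduced; an SD of about 1.5 would give it. That is a separate matter. I keep 36 per arm because it is the planned evaluable number.

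**Step 2: the spread each analysis works with.**

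- Change score: s = SD × √(2(1 − ρ))
- ANCOVA: s = SD × √(1 − ρ²)
- Follow-up score alone: s = SD

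The variance ratio of ANCOVA to change score is (1 + ρ)/2, that is 0.65, 0.75 and 0.85 at ρ 0.3, 0.5 and 0.7.

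**Step 3: power by formula.** Power = Φ(1/(s√(2/36)) − 1.96). At ρ 0.3:

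- Change score: s = 1.36 × √1.4 = 1.609; standard error 0.379; Φ(2.637 − 1.96) = 75.1%.
- ANCOVA: s = 1.36 × √0.91 = 1.297; standard error 0.306; Φ(3.270 − 1.96) = 90.5%.

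At ρ 0.5 the pair is 87.7% and 95.0%; at ρ 0.7 it is 98.1% and 99.2%. With SD 1.5 the three pairs are 66.7% and 84.3%, 80.7% and 90.4%, 95.5% and 97.7%.

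**Step 4: the conditional rule, by simulation** (40,000 trials per scenario; t-based, so slightly below the formula). ANCOVA is used if the trigger fires, otherwise a t test on change.

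| ρ | Change score only | Conditional, p<0.05 trigger | Conditional, imbalance >0.2 SD | ANCOVA in all cases |
|---|---|---|---|---|
| 0.3 | 74% | 75% | 82% | 90% |
| 0.5 | 87% | 88% | 91% | 94% |
| 0.7 | 98% | 98% | 99% | 99% |

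The p<0.05 trigger fires in about 5% of trials and the 0.2 SD trigger in about 39%. An unadjusted t test on follow-up scores has about 87% power at every ρ.

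**Step 5: type I error.** Under the p<0.05 trigger it is 4.0%, 4.3% and 4.7% at ρ 0.3, 0.5 and 0.7. Across both triggers it stays below 5%, with a low of about 3.3%.

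**Step 6: imbalance left in the estimate.** The baseline difference has standard error 1.36 × √(2/36) = 0.32 points, so differences up to 1.96 × 0.32 = 0.63 points pass a p<0.05 trigger. The change-score difference then carries an error of (ρ − 1) × imbalance. At the 0.63 limit this is 0.44, 0.31 or 0.19 points in size for ρ 0.3, 0.5 and 0.7, against a 1-point target. Under the 0.2 SD trigger the limit is 0.2 × 1.36 = 0.27 points, and the error at most 0.19, 0.14 or 0.08.

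**The case against.** The strongest reply is that the large figures come from choices the article does not make.

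- **Correlation.** ρ is not given. At 0.7 the loss is about 1 point of power. On the stated SD, the change-score test already reaches 80% power at ρ of about 0.4 or more. This stands: a shortfall against the planned power appears only at low ρ.
- **Trigger.** The p<0.05 threshold is assumed. A 0.2 SD trigger recovers roughly half of the gap at ρ 0.3 and 0.5. This stands too, and it also shows that what the rule does cannot be known from the text.
- **What is tested.** Data Analysis does not say in words that the t test is run on change; that is read from it together with Outcome Measures. If follow-up scores are tested instead, the loss at ρ 0.3 is only 2 to 3 points, but it grows with ρ (87% against 99% at 0.7).
- **Repeated-measures ANOVA.** VAS is measured at many visits, so this test may apply. With baseline as one of only two time points it tests the same contrast as the change score; with more visits the figures above do not describe it. No baseline covariate is stated there either.
- **Timing.** The Results section reports data cleaning as complete, and the abstract says that analysis is ongoing, so a new model now could look post hoc. This is a real cost, and calls for dating and disclosure.

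A reader might also infer that choosing the model from the data produces false positives, or that the change score is biased. Neither is supported. Type I error in the simulations is at or below nominal, and the change score is unbiased over all randomisations. The errors in step 6 are conditional on the imbalance that happened to occur.

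**Conclusion.** The point holds as one of efficiency and clarity, not validity. The article makes baseline adjustment depend on an undefined trigger, and adjusting in all cases did at least as well in every scenario computed. The loss of power from testing change scores under a p<0.05 trigger is about 15 points at ρ 0.3, 6 at 0.5 and 1 at 0.7, and less under a looser trigger. These sizes rest on equal SDs of 1.36, 36 per arm, a 1-point difference and a single-visit comparison. A reader might take the 15-point loss as the expected one; without a stated ρ or trigger, the documents do not support singling it out.

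**What to change.** Before the between-group analysis is run, replace the conditional ANCOVA sentence in Data Analysis with:

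> The between-group analysis of VAS, ODI and SF-36 will be adjusted for the baseline value of the outcome (ANCOVA or a mixed model with baseline as covariate) in all cases, whatever the observed baseline balance.

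This needs no new data and costs one model parameter. Under Protocol Amendments, a change to the analysis methods is reported to the sponsor and the ethics committee with its reasons. Because it follows data cleaning, it should be dated, should state whether any comparison by arm had been seen, and should be disclosed in the final report. The acute, subacute or chronic category recorded at baseline could be added as a covariate, but nothing in the article shows that it is prognostic, so it is optional and not part of this fix.
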